#### Sample size

The sample size of patients to be recruited for the trial evaluation is calculated on the basis of the primary outcome measure above. Our previous study [18] estimated that the number of days of antibiotic use by symptomatic RTI patients was 4.35 $$\pm$$ 2.06 for rural township health centers in Anhui province. There is no internationally agreed minimally important difference in the days of patients using antibiotic. However, we anticipate that a reduction of at least 15% in the days of antibiotic use would represent a meaningful change at the population level. So, we assume the following: (1) the intervention group is 20% lower than the control group, i.e., a reduction of about 0.87 days; (2) standard deviation of the days of antibiotics use is 2.06 days; and (3) the alpha value is 0.05. Given these, to detect a possible absolute difference of 0.87 days in the rates with 90% power, we will need 118 RTI patients in each arm. Based on our previous study results the estimated design effect value would be 2.45. By allowing for a 20% attrition rate and for a 20% loss to follow-up rate, therefore we would aim to recruit at least 2.45×118×2×1.2×1.2=833 patients into the study and this translates into about 35(833/24=35) patients per township/community health center.

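### The sample size multiplies by 1.2 twice for two 20% losses where its own inputs call for division by 0.8 twice: 904 patients, not 833

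*Protocol article*

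**What the plan says.** The calculation is in the Sample size section of the protocol article. It rests on a previous study, which "estimated that the number of days of antibiotic use by symptomatic RTI patients was 4.35" with a standard deviation of 2.06. It assumes that "the intervention group is 20% lower than the control group, i.e., a reduction of about 0.87 days", that the "standard deviation of the days of antibiotics use is 2.06 days" and that "the alpha value is 0.05". From these it states that, "with 90% power, we will need 118 RTI patients in each arm".

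A design effect of 2.45 is taken from earlier work, with no ICC or cluster size given. The section then continues "By allowing for a 20% attrition rate and for a 20% loss to follow-up rate" and reaches the target: "therefore we would aim to recruit at least 2.45×118×2×1.2×1.2=833 patients into the study". This total is divided over 24 centres as 35 each. The Patient recruitment section repeats 35 per centre, so 24 × 35 = 840 is the operational target. The section on allocation confirms 6 counties with 4 centres each, 2 per arm within each county, so 12 centres per arm.

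**The concern.** To have N patients left after losing 20%, one recruits N/0.8 = 1.25N. Recruiting 1.2N leaves 0.96N. Applied twice, the printed factor of 1.44 leaves 1.44 × 0.64 = 0.92 of the number required, so the target is about 8% too small for the losses named in the same sentence.

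The printed formula sets the recruitment target and supports the 90% power claim. If power is overstated, a null result would be read as stronger evidence against a 0.87-day effect than the design supports.

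**Working it through.** **Inputs, all from the Sample size section unless noted.** Difference 0.87 days (20% of 4.35); SD 2.06; alpha 0.05; power 90%; design effect 2.45; losses of 20% and 20%; 24 centres (also in the allocation section); 35 patients per centre. The sidedness of alpha is not stated. I assume two-sided, which reproduces the plan's figure.

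**Step 1, reproduce the plan.**
- n per arm = 2 × (1.96 + 1.2816)² × 2.06² / 0.87² = 117.8, so 118. Agrees.
- Analysable total = 118 × 2 × 2.45 = 578.2.
- Plan's inflation: 578.2 × 1.2 × 1.2 = 832.6, so 833. Agrees.

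**Step 2, correct the loss step.**
- Share retained = 0.8 × 0.8 = 0.64.
- Required recruitment = 578.2 / 0.64 = 903.4, so 904; 904/24 = 37.7, about 38 per centre.
- Shortfall = 904 − 833 = 71; 71/904 = 8%.
- What the plan's target leaves: 833 × 0.64 = 533, or 840 × 0.64 = 538, against the 578 needed.

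**Step 3, power for 0.87 days at 840 enrolled, both losses occurring, design effect held at 2.45.**
- Effective n per arm = 840 × 0.64 / 2 / 2.45 = 109.7.
- SE = 2.06 × √(2/109.7) = 0.278; 0.87/0.278 = 3.13.
- Normal quantiles (the plan's method): 87.9%.
- Noncentral t, 22 df (24 centres − 2): 84.8%.
- Noncentral t, 17 df (also fitting the 6 counties): 83.8%.
- For comparison, with all 578 patients retained: 90.0% (normal), 87.3% (22 df).

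The loss slip alone costs about 2 points on the plan's own method. Most of the fall to about 85% comes from the t reference.

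**Step 4, sensitivity at 840 enrolled.** The source of 2.45 is not given, so the ICCs below are assumptions, from ICC = (2.45 − 1)/(m − 1) for cluster size m. With both losses, 35 × 0.64 = 22.4 patients per centre are analysed.

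| Assumption | Analysed | Design effect | Power, normal | Power, 22 df |
|---|---|---|---|---|
| 2.45 held fixed, both losses | 538 | 2.45 | 87.9% | 84.8% |
| 2.45 belongs to about 24 per centre (ICC about 0.063), both losses | 538 | 2.34 | 89.2% | 86.4% |
| 2.45 belongs to 35 per centre (ICC about 0.043), both losses | 538 | 1.91 | 94.3% | 92.2% |
| 2.45 held fixed, one 20% loss only | 672 | 2.45 | 93.8% | 91.6% |

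**Step 5, added information on the 15% reduction.** 0.15 × 4.35 = 0.65 days. Power on 22 df at 840 enrolled with both losses is about 61% (design effect 2.45) to about 72% (design effect 1.91).

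**The case against.** The strongest reply is that the documents do not settle whether power is below 90%. Without the ICC and cluster size behind 2.45, one cannot say that it applies to 22.4 analysed patients per centre. If it was derived for 35, the smaller analysed clusters carry a smaller design effect and power exceeds 90%. The two losses are also not defined and may overlap; with only one, power again exceeds 90%. Multiple imputation is planned, and the outcome is built from several interviews, so a missed call need not remove a patient. All of this stands and makes the power shortfall conditional. It does not rescue the printed formula, which applies 2.45 before the loss inflation and makes a separate allowance for each loss.

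The 22 df step can also be challenged. It is a refinement for few clusters and not a correction of arithmetic, and the Data analysis section names an independent-samples t-test, not a cluster-level one. That is fair, so both figures are given.

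Two stronger readings are tempting and are not supported. A reader might infer that the calculation ignores its 24 clusters. It does not: a design effect is applied and the total is spread over 24 centres; only a small-cluster degrees-of-freedom allowance is absent. A reader might also take it as an error that the plan says "we anticipate that a reduction of at least 15% in the days of antibiotic use would represent a meaningful change" yet powers for 20%. A 20% reduction meets that threshold, 90% power is claimed only for 0.87 days, and powering on an anticipated effect above the smallest meaningful one is a design choice.

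**Conclusion.** The loss inflation is wrong as written. For two separate 20% losses, with 2.45 used as the plan uses it, the recruitment figure should be 904 and not 833. This rests only on numbers printed in the section.

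The consequence for power is modest and conditional. If both losses occur and 2.45 holds for the analysed patients, power for 0.87 days at 35 per centre is about 88% (normal) or about 85% (22 df). A reader might infer that 90% is definitely not reached; the documents do not support that, because power is about 92% on 22 df if 2.45 belongs to 35 per centre or if only one loss occurs. Nor would 904 restore 90% by the stricter standard: it leaves 578 analysable patients and 87.3% on 22 df. With 2.45 fixed, 90% on 22 df needs 634 analysed, or 634/0.64 = about 991 recruited.

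**What to change.** Replace the factor 1.2 × 1.2 by division by 0.8 × 0.8, giving 118 × 2 × 2.45 / 0.64 = 904, about 38 per centre. Give the ICC and cluster size behind 2.45, and say whether attrition and loss to follow-up are separate, so that the power can be confirmed.

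If enrolment stays at 35 per centre, restate the power for 0.87 days as about 88% (normal) or about 85% (22 df), or as the figure that follows once the basis of 2.45 is known. Power for 0.65 days may be added for information.

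Restating costs a rewording of one paragraph and a slightly less favourable power figure, with no extra patients. Adopting 904 means recruiting 71 more than the stated 833, about 3 more per centre. The Trial status section anticipates recruitment until 30/12/2026.

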#### Eligibility criteria

The inclusion criteria for patients are presenting males or females to the site health centers who are (1) 18 years or older and able to give consent to participate in the patient survey and/or follow-up interviews; (2) diagnosed, by doctor, with common RTIs, including acute upper RTI, common cold, acute bronchitis/tracheitis, exacerbation of chronic obstructive pulmonary disease, and influenza-like illness; and (3) able to receive and comprehend messages via either self-reading or assistance from family members. Exclusion criteria are patients who (1) have previously sought treatment for the current illness from the participating health centers and (2) are pregnant individuals.

#### Patient recruitment

In order to evaluate the trial, 35 patients diagnosed with RTIs from each of the site township or community health centers will be recruited using a consecutive strategy. More specifically, each of the health centers in the intervention and control arms will be sent one investigator and from the start date when he/she arrives at the site, all incoming patients with RTIs will be invited to participate after consultation until a preset number of eligible patients have been recruited. The field investigator will conduct the recruitment face-to-face after obtaining informed consent from participants.

#### Data collection

The study data will be collected through one baseline and five follow-up telephone interviews. For any recruited patient, the baseline interview happens immediately after the consultation, while the follow-up interviews are scheduled at 7, 14, 21,180, and 365 days after the baseline. The interviews will be performed by trained data collectors using a structured questionnaire adapted from our previous study [18] (Additional files 1, 2, 3 and 4). The main content of the questionnaire includes patient demographic characteristics (e.g., sex, age, education, residential area, and medical insurance status), illness duration, symptoms, severity rating, diagnosis, antibiotics, and other medicines prescribed. EPI DATA 3.1 will be used to create a data entry interface for all the on-site and telephone follow-up interviews. Table 3 summarizes measure by measure time schedule for data collection.

**Table 3 Tab3:** SPIRIT schedule of outcome measures

**Category**	**Outcome measure**	**Initial consultation**	**Days after consultation**				
			**7**	**14**	**21**	**180**	**365**
Primary measure	Number of days with antibiotics use	√	√	√	√		
Secondary measures	Illness duration	√	√	√	√		
	Illness severity	√	√	√	√		
	Times of re-visits				√		
	Antibiotics re-prescription				√		
	Knowledge about and attitude toward antibiotics					√	√
	Times of re-occurrence of RTIs					√	√
	Health service seeking for re-occurred infections					√	√
	Antibiotics consumption for re-occurred infections					√	√
	Quality of life (EQ-5D-5L)	√	√	√	√		
	Attitude toward intervention messages		√	√			
	Understanding of intervention messages		√	√			

#### Data quality control

All field and telephone interviewers will be trained on the content of the face-to-face and telephone interviews and principles and tips for performing the interviews before data collection. Embedded logical examinations will be designed into the aforementioned EPI DATA data entry tool to prevent missing fields and out-of-range values. All interviews will be, after informed consent, audio recorded to allow for later self and independent quality checks. An experienced data quality supervisor will be assigned to perform daily quality examinations of a random sample of 10% of all the questionnaires administered during the day. Failed follow-up interviews will be re-attempted up to 3 times in the following 3 days at different hours with reasons being clearly recorded for each of the failures.

#### Data protection

All of the patients recruited in this study will be identified by a unique number. The patient number will be assigned to each participant once they have been recruited into this study. This patient number will be used from that point forward on all follow-up data. The hard copy documents of the study, including the informed consent of the patients and the project implementation diary, will be kept in locked files in the offices of the project assessment supervisor and the Principal Investigator. The electronic files, including the original EPI DATA files and Excel files, and interview recordings, will be backed-up on separate media and stored in a secure fling cabinet. Personal identifier will not be stored in the data set. Access to security passwords will be given only to the Principal Investigator and the Assessment Supervisor from the center of health management and technology, Anhui Medicine University. The center is independent from the sponsor and has no competing interests. Audits will be conducted by a dedicated team from the Health Sciences Division of Anhui Medical University to ensure data security conduct is adhered to.

#### Data analysis

The data collected will be used to compare the differences between the control and intervention groups as a whole and between subgroups in the intervention arm in terms of days of antibiotic use per episode of RTIs; times of re-visits to clinics and antibiotics re-prescription for the same RTI; quality of life; times of re-occurrence of RTIs and related health service seeking and antibiotics consumption for re-occurred infections; and scores of patients’ knowledge about and attitude toward antibiotics.

Estimation of statistical significance and confidence intervals will assume a type I error established in alpha=0.05, using the IBM SPSS V25 statistics package. Missing data will be treated as missing at random and imputed using a chained-equations multiple imputation model. Initial data analysis will consist of descriptive summaries intended to examine the patterns of the various measurements and check for normality of the continuous variables. And necessary transformations will be explored and selected, if necessary, to induce approximate normality. Regarding the numerical variables between two groups, *t*-test of independent samples for mean comparisons will be carried out. The chi-square test will be conducted for categorical variables (non-continuous). Lastly, no interim analysis is planned.

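### Subgroups are to be compared inside the intervention arm, with no control counterpart and no descriptive label, so the contrast cannot show in whom the messages work

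*Protocol article*

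**What the plan says.** The first sentence of the Data analysis section plans an overall comparison of the two arms. To this it adds a second comparison, "between subgroups in the intervention arm in terms of days of antibiotic use per episode of RTIs". Further outcomes follow: re-visits, re-prescription, quality of life, recurrence and the knowledge and attitude scores. So two kinds of comparison are planned for the same outcomes: arm against arm overall, and subgroup against subgroup within the TMP arm.

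The section sets alpha at 0.05 and gives the tests: "Regarding the numerical variables between two groups, *t*-test of independent samples for mean comparisons will be carried out", and chi-square tests for categorical variables. Nothing separates the subgroup comparison from these tests or marks it as descriptive or exploratory.

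No part of the article defines the subgroups, says what the comparison is for, or plans a TMP-UC contrast within subgroups or an arm-by-subgroup interaction. The Objectives are framed as TMP against usual care.

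**The concern.** Randomisation protects the comparison between arms. It does not protect a comparison of one kind of TMP patient with another, because such patients may differ in antibiotic use whatever the messages do. Three features of this trial make that concrete:

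- Table 2 counts antibiotic days from illness onset to the initial consultation in the primary outcome. Those days precede every message, yet they enter any within-arm subgroup difference.
- The Eligibility criteria run from common cold to exacerbation of chronic obstructive pulmonary disease, and the Message tailoring section gives each diagnosis its own normal duration. Prognostic gaps between subgroups are plausible.
- If the subgroups are formed by reading or understanding the messages, they arise after allocation and are self-selected.

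The Conclusion says that the trial should show how the messages can be improved and should inform scale-up. A within-arm difference taken as evidence of differential effect could steer those decisions wrongly, although a randomised contrast is available for any subgroup defined at baseline.

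**Working it through.** **Inputs (Sample size section).** "the alpha value is 0.05"; "standard deviation of the days of antibiotics use is 2.06 days"; "the intervention group is 20% lower than the control group, i.e., a reduction of about 0.87 days"; power 90%; 118 patients per arm before a design effect of 2.45.

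**The plan's own figure.** n per arm = 2 × (1.960 + 1.282)² × 2.06² / 0.87² ≈ 118 (two-sided). Then 2.45 × 118 × 2 × 1.2 × 1.2 = 832.6, or 833. Both reproduce.

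**What each contrast estimates.** Let g be the gap in antibiotic days between subgroups 1 and 0 under usual care, Δ the benefit in subgroup 0, and Δ + δ the benefit in subgroup 1.

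- Subgroup difference in the UC arm: g
- Subgroup difference in the TMP arm: g − δ
- Interaction (TMP-arm difference minus UC-arm difference): −δ

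The within-arm contrast returns g − δ, and without the UC arm the two parts cannot be told apart.

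**Illustration.** Assumptions that are not in the article: two equal subgroups, and the values of g. The effective sample is taken as 118 per arm (the plan's 2.45 × 118 = 289 per arm, divided by 2.45), so 59 per subgroup and arm.

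- SE within arm = 2.06 × √(2/59) = 0.379 days
- SE of interaction = 2.06 × √(4/59) = 0.536 days

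With the same benefit in both subgroups (δ = 0), the chance of a significant result at two-sided 0.05 is:

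| Gap g (days) | g / 0.379 | Within-arm test | Interaction test |
|---|---|---|---|
| 0.5 | 1.32 | 26% | 5% |
| 0.87 | 2.29 | 63% | 5% |
| 1.0 | 2.64 | 75% | 5% |

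A simulation of 20,000 trials gave 63.2% and 5.2% at g = 0.87, and 75.4% and 5.1% at g = 1.0.

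**The error in the other direction.** Suppose that the subgroup that uses 0.87 days more anyway also gains an extra 0.87 days from the messages. The within-arm contrast is then 0.87 − 0.87 = 0. In simulation it was significant in 5.3% of trials, and the interaction test in 37.7%.

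**Power of the interaction test.** For δ = 0.87: 0.87 / 0.536 = 1.62, and Φ(1.62 − 1.96) ≈ 0.37.

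**Sensitivity to the design effect.** The full 2.45 may be too severe for subgroups that cut across health centers. At the other extreme, with no design effect (289 per arm), the standard errors are 0.242 and 0.343. The within-arm test is then significant in 54%, 95% and 98.5% of trials for the three gaps, and the interaction power is about 72%.

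**The case against.** The best defence is that the comparison is about process. The article collects understanding of and attitude toward the messages at days 7 and 14, records how often doctors deliver the package, and lets doctors edit the templates. Subgroups built on these exist only in the TMP arm, which would explain the wording, and no interaction with arm can be fitted for them. The article is also a condensed account, and subgroup definitions commonly belong in the analysis plan.

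Much of this stands. Undefined subgroups are not the complaint here, and on the process reading the remedy is a label, not a new model. But that reading does not let the contrast show a message effect either: patients who read or understand more are self-selected. Nor is this only missing detail, since the sentence itself places the comparison in one arm, for the primary outcome, without a descriptive label.

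Four stronger readings are tempting, and the article does not support them:

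- A reader might infer that the trial will report the messages as working better in some patients. No stated aim or outcome says so.
- A reader might infer that the contrast shows only who uses more antibiotics anyway. It also contains any real difference in effect; the fault is that the two are mixed.
- A reader might infer that between-arm subgroup analyses are ruled out. They are not mentioned, which is different.
- A reader might assume a very large gap. With 833 × 0.8 × 0.8 = 533 evaluable patients, about 133 per subgroup and arm, a 2-day gap gives t = 2 / (2.06 × √(2/133)) ≈ 7.9, or about 5 after dividing by √2.45. But 2 days is 46% of the 4.35-day mean, and nothing in the article supports so large a gap.

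**Conclusion.** The concern holds in limited form. As written, the subgroup comparison cannot show in whom the messages work, whether the subgroups are defined at baseline or after allocation. If it is read as effect modification, it can mislead in both directions. With an effective 118 per arm and equal subgroups, a prognostic gap of 0.5 to 1.0 day produces a significant difference in about 26% to 75% of trials with identical benefit, and a true extra benefit can be cancelled out. The gaps and the equal split are assumptions; the mixing of prognosis and effect depends on neither.

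Whether misreporting would follow is unknown, because the purpose is not stated. The overall TMP-UC comparison, the sample size and the stated objectives are unaffected. The change should be made, but it does not threaten the trial's main conclusion.

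**What to change.** Replace the within-arm subgroup clause with two statements.

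- For subgroups defined at baseline (for example diagnosis, age and education), estimate the TMP-UC difference within each subgroup, with its confidence interval, and the arm-by-subgroup interaction. Use both arms and a model that accounts for health-center clustering, and label the analysis exploratory.
- Comparisons among TMP patients by reading, understanding or delivery of the messages are descriptive only and are not evidence of a message effect.

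No new data are needed: the questionnaire covers diagnosis, age and education for recruited patients in both arms, and the primary outcome is compared across both. The text change is short, but the Data analysis section now names only t-tests and chi-square tests, so a model that allows for clustering has to be added. The other cost is precision: the interaction standard error is √2 times the within-arm one (0.536 against 0.379 days). Power for a 0.87-day interaction with two equal subgroups is about 37%. The plan should say so, and should say that a non-significant interaction does not show a uniform effect.

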**Primary measure**	
-Number of days with antibiotics use	Days of antibiotics use from onset of the RTI to the initial consultation + days of antibiotics use from day 1 to 21 after the initial consultation based on the patient’s responses to question item A5d in Additional file 1, B2 in Additional file 2, and item C2-C4 in Additional file 3. Here, days of antibiotics use is defined as days on which the patient has used any antibiotics.

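### The scale of the primary analysis is left to a data-driven transformation, although the objective, outcome and sample size are all in untransformed days

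*Protocol article*

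**What the plan says.** The first objective is a shorter duration of antibiotic use in the message arm than under usual care. Table 2 makes the primary measure a patient-level count, in which "days of antibiotics use is defined as days on which the patient has used any antibiotics", from onset of the infection to day 21 after the consultation.

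The Sample size section works on the same scale. It takes from an earlier study that "the number of days of antibiotic use by symptomatic RTI patients was 4.35", assumes that "standard deviation of the days of antibiotics use is 2.06 days", and sets the effect so that "the intervention group is 20% lower than the control group, i.e., a reduction of about 0.87 days". It also names a reduction of at least 15% in days as meaningful for the population.

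The Data analysis section sets a sequence: descriptive summaries and a normality check on the collected data, then "necessary transformations will be explored and selected, if necessary, to induce approximate normality", then an independent-samples t-test for numerical variables. It gives no trigger, no list of candidate transformations and no exception for the primary outcome. The Blinding section keeps the analysts blind to allocation until the quantitative analysis is complete.

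**The concern.** The trial is designed "to detect a possible absolute difference of 0.87 days". A t-test on log(1 + days) or on the square root of days compares the means of those quantities instead. Two arms can have the same mean number of days and different mean logs, so the null hypothesis changes. The estimate can no longer be read against 0.87 days or against the 15% threshold (0.15 × 4.35 = 0.65 days).

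The scales part company mainly when some patients use no antibiotics. Such patients sit at zero, and a log or square root gives the gap between zero and a few days more weight than a shortening among users. The Background section puts antibiotic use at over 80% of patients with symptomatic infections, so some zeros are plausible. Several messages in Table 1 aim at delaying or avoiding antibiotics, so the intervention may change their share.

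At stake is whether the primary result answers the question that the trial was sized for.

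**Working it through.** **1. The plan's own figure.** Inputs from the Sample size section: difference 0.20 × 4.35 = 0.87 days, SD 2.06, alpha 0.05 (two-sided reproduces the figure), power 90%.

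n per arm = 2 × (1.960 + 1.282)² × 2.06² / 0.87² = 2 × 10.51 × 4.244 / 0.757 = 117.8, so 118.

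Total = 2.45 × 118 × 2 × 1.2 × 1.2 = 832.6, so 833. Both figures reproduce, and both rest on untransformed days.

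**2. How many zeros are possible.** The share is not given. If 4.35 ± 2.06 describes all patients, the largest possible share is r/(1 + r) with r = (2.06/4.35)² = 0.224, which is 18.3%. If it describes users only, 20% zeros would give a mean of 0.8 × 4.35 = 3.48 days and an SD of √(0.8 × 2.06² + 0.2 × 0.8 × 4.35²) = 2.53.

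**3. Effect of the scale.** Assumptions: users' days are gamma-shaped and rounded to whole days; 118 effective patients per arm; patients independent. Entries are the chance of a significant result in favor of the messages.

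| Control vs message arm | Raw days | log(1+x) | Square root |
|---|---|---|---|
| No zeros; days 20% lower | 0.89 | 0.96 | 0.94 |
| 20% zeros in both; users' days 20% lower | 0.58 | 0.41 | 0.37 |
| Zeros 20% vs 36%; users' days equal | 0.53 | 0.71 | 0.71 |
| Equal mean days; zeros 20% vs 35%; users' mean 4.35 vs 5.35 | 0.02 | 0.23 | 0.21 |

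In the first three rows direction agrees and only power differs. In the fourth, mean days are equal (3.48 vs 3.49), so the raw test stays near its nominal level while the others respond to a difference in shape.

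**4. When direction changes.** If one arm's distribution lies at or below the other's throughout, every increasing transformation gives the same sign. A reversal needs distributions that cross:
- Zeros 20% vs 40%, users' mean 4.35 vs 6.2 days: raw difference +0.24 days, log difference −0.15.
- Zeros 25% vs 10%, users' mean 5.0 vs 3.7 days: raw −0.42 days, log +0.09.

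In both, non-use and length of use move in opposite directions.

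**5. Would the plan's criterion pick such a scale?** It depends on the shape.
- Matched to 4.35 ± 2.06 with 10% zeros (users' mean 4.83, SD 1.54), control skewness is about −0.3 raw and −1.8 after log(1+x). The log makes normality worse.
- With more right-skewed use (users' mean 4.35, SD 3.0; zeros 20% vs 35%; equal mean days), skewness pooled over arms falls from about 1.4 to about 0 on the log or square-root scale, so the criterion would favor one of them. In shapes of this kind the transformed tests reject in about 18–22% of trials, against 5% on raw days. The control SD here is √(0.8 × 3.0² + 0.2 × 0.8 × 4.35²) = 3.20, above the planned 2.06.

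**6. Is a transformation needed?** With 10–40% zeros, the raw t-test's type I error was 0.047–0.050 in 8,000 simulated comparisons per setting. Normality of the day counts is not needed to compare means at this size.

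**The case against.** The strongest reply is that the sentence is generic and conditional. It follows a check of continuous variables, covers many measures, and acts only where a transformation brings the data closer to normal. Under the distribution closest to the planning figures (10% zeros), log and square root move away from normality, so an analyst following the rule would leave the days alone. The power figures under that distribution (94% raw against about 60% log when all use shortens by 20%; about 82% against 93% when non-users rise to 28%) then describe a choice that the rule would probably not make. Where the log clearly helps and there are no zeros, the scales agree. The analysts are also blind to allocation, and details of the trigger could sit in an analysis plan that is not shown.

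Much of this stands. The power figures matched to the planning values should not be read as the expected harm. Blinding limits choosing a scale to favor an arm; even choosing the best of three p-values would raise type I error only to about 0.065–0.068.

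Three things remain. The section sends numerical variables in general to the t-test, and nothing exempts the primary outcome. For plausible right-skewed use with zeros, the criterion does point to a transformation. And blinding does not turn a test on a transformed scale back into one about mean days. This is also more than missing detail: the article states a rule that does not fit its own objective and sample size.

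**Conclusion.** The point holds in a limited form. The protocol lets the scale of the primary analysis be chosen from the data, while everything that defines the primary question is in days. If a log or square-root scale were chosen, the hypothesis would change and no difference in days would be estimated. Depending on the share of zeros and the shape of use, power and significance could shift in either direction, as the table shows.

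A reader might infer three stronger things that the documents do not support:
- That the outcome is known to be zero-inflated. No section says so; the share of zeros is an assumption here, capped at 18.3% if the planning mean and SD cover all patients.
- That transforming would generally reverse the conclusion. Direction changes only when non-use and length of use move in opposite directions.
- That the 18–23% rejection rates with equal mean days are ordinary false positives. The arms differ in those scenarios, only not in mean days.

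All simulated figures assume gamma-shaped use among users and 118 effective, independent patients per arm. The reproduced sample size needs no assumption about shape.

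**What to change.** In the Data analysis section, exempt the primary outcome from the transformation step. State that days of antibiotic use are analyzed untransformed, as a difference in means with a 95% confidence interval, by a method that allows for clustering by health center. Report the proportion of patients with zero antibiotic days by arm alongside. Keep transformed-scale or count models, if wanted, only as prespecified sensitivity analyses.

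The scale statement costs a sentence or two and an amendment by the route that the protocol describes. It needs no new data and no extra patients: 118 per arm before inflation and 833 in total stand, because they were computed on this scale. The section names no clustered method, so that choice has to be written down too; it goes with the design effect of 2.45 already in the sample size. The change should be made before the outcome data are examined.
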